### Randomisation

In this study a cluster design is used because the intervention is delivered to groups. To minimise contamination, the unit of randomisation will be the PHCC. Those PHCCs who agree to participate will be randomly allocated to control or intervention groups by a random sequence generated by a computer programme in blocks of random size and prepared before recruitment of the PHCC by an independent statistician who will be blind to the PHCCs' identities. The blocking factor was randomly selected between an even number (e.g., 4, 6, or 8) and will vary as the recruitment continues. Primary care physicians will be informed about their allocation after giving final consent to participation.

To minimise imbalance across intervention groups, randomisation was conducted stratifying by percentage of immigrants from developing countries registered in each district. We consider two strata, less than and more than 15% immigrants. This variable is taken as a proxy of socioeconomic level.

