### Sample size

The sample-size calculation is based on change in RDQ at three months after onset of LBP. It is recommended that a change in 2 to 3 points on the RDQ should be considered the minimum clinically important change [22]. To allow for the cluster randomisation by PHCC, we assume an intraclass correlation coefficient of 0.1 [34] and a minimum average number of individuals sampled per PHCC of 25. In order to detect a difference of 2.5 points between the two intervention arms with a standard deviation of 5.7 [22,35], an alpha error of 0.05, a beta error of 0.10, and a 20% dropout rate, a sample size of 932 subjects was required, 466 subjects per intervention arm. Therefore, the total number of PHCCs is 38 (19 for group).

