### Statistical Analysis

Data will be analysed in accordance with CONSORT guidelines, extension to cluster randomised trial. Data will be analysed by intention-to-treat. To address potential biases due to incomplete follow-up, we will analyse patients with complete data at all time points and those with data at any time point, using the last known value carried forward to replace missing values. Bias due to non-response will be assessed at each follow-up.

The primary end points for the trial will be 3 months (short term), 6 months and 12 months (long term).

We will obtain descriptive statistics for the outcome measures, baseline characteristics and clinical measures as mean (standard deviation) or numbers (percentages), with 95% confidence intervals at each assessment for all the patients and for each group.

The distribution of data will be checked to ensure that parametric assumptions are met, and non-parametric analyses will be used when appropriate. We will use independent *t *tests or Mann-Whitney U tests for continuous data and Χ^2 ^tests or Fisher's exact probability test for categorical data for unadjusted comparisons between groups at each assessment.

Continuous data for change in scores from baseline will be compared between groups and for each group. The paired t-test for difference will be used to compare the change between pre- and post- intervention.

To decide on an important change in individuals, we will contrast the distributions of changes in all the questionnaires and in each assessment, in individuals who change to chronic state and in individuals who do not [22]. We will do the same between those individuals who return to work and those who do not. We will compare individual change scores to the standard error of measurement (SEM).

To detect changes in groups, the intervention effect will be calculated through the effect-size for each questionnaire and at each assessment. Effect-size was calculated following the method of Kazis et al [36]

We will evaluate responsiveness of each scale by standardised response mean (SRM) [37] and receiver-operating characteristic method (ROC curve). The SRM will be performed between two-time points (baseline and each assessment) and for each intervention arm. We have chosen recovery according to the patient as an external criterion for clinically relevant improvement.

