Simple correlations between the scores of the different scales (disability, severity of pain, quality of life and psychosocial scales) will be obtained through the Pearson linear correlation coefficient or the Spearman correlation, in the case of parametric assumptions not being met, at each assessment.

Since the unit of randomisation is the PHCC, we will use a regression analysis of individual level data using methods for clustered data [38]. For adjusting comparisons and to account for cluster randomisation, multilevel linear regression analyses on repeated measures on each of the outcome scales will be used to assess the effect of intervention and to investigate the factors that influence each of the outcome scales at each time point adjusting for baseline scores, baseline characteristics of patients (socio-demographic, clinical and professional) and the other scale scores if they are found to affect outcomes significantly over time. The possible association between intervention and time will be studied. The PHCC and the individual will be considered as random effects and intervention and time as fixed effects.

A multilevel Cox regression model will be used to evaluate the association between the main independent variable, the prognostic factors and the time of subsiding of the current episode of LBP or return to work at 3 months. The patients for whom the duration of the current episode is more than 3 months or those who do not return to work at 3 months will be censored at that time. Kaplan-Meier survival curves will be used to compare the rate of evolution to chronicity and return to work between both groups. Logrank and Breslow test will be used for testing the equality of survival among groups.

The differences in medication prescription at baseline and at each assessment in the interventions and control groups will be compared.

We will calculate the relative risk reduction (RRR) and number needed to treat (NNT) to facilitate development of clinical guidelines for future management.

We will study the interactions and the collinearity. The collinearity of the maximal models will be evaluated using the criteria proposed by Belsley [39]. The significance level of all models will be set at 5%.

The SPSS statistical package for Windows, version 17 (SPSS Inc., Chicago, IL) and the SAS 9.1.3 for Windows (SAS Institute Inc., Cary, NC, USA), will be used for statistical analysis.

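### Patient-level between-arm tests that ignore clustering are listed beside the multilevel models with no rule on which governs, and they are the only named tests for binary outcomes

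*Protocol article*

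**What the plan says.** The Randomisation section states that "the unit of randomisation will be the PHCC". The Sample size section follows this through: "we assume an intraclass correlation coefficient of 0.1", together with "a minimum average number of individuals sampled per PHCC of 25".

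The Statistical Analysis section then describes two layers of between-arm comparison.

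- **Patient-level tests.** Continuous data are compared by independent t or Mann-Whitney tests. Categorical data are compared by chi-square or "Fisher's exact probability test for categorical data for unadjusted comparisons between groups at each assessment". For time to event, Kaplan-Meier curves are compared between arms, and "Logrank and Breslow test will be used for testing the equality of survival among groups". No cluster version of any of these tests is named.
- **Clustered models.** Multilevel linear regression on repeated measures, with centre and individual as random effects, is planned for each outcome scale, expressly to allow for cluster randomisation. A multilevel Cox model is planned for the end of the pain episode and return to work, censored at 3 months. A general sentence says that regression on individual data will use methods suited to clustering.

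The section also plans RRR and NNT, and a comparison of medication prescription between arms at each assessment, without naming a method for either. It commits the analysis to the CONSORT extension for cluster trials.

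**The concern.** The listed tests, as ordinarily defined, treat patients from one centre as independent. The Sample size section assumes that they are not. A test that ignores a positive ICC understates the standard error of the arm difference, so its p-values are too small.

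Three things are at stake:

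1. For the outcome scales and the time-to-event outcomes, the report would carry two sets of p-values, one valid and one not. The plan has no rule for the case where they disagree.
2. For sick leave (yes/no), a listed secondary outcome, and for medication prescription, chi-square or Fisher is the only named test. An invalid p-value could stand alone there.
3. RRR and NNT are meant to inform clinical guidelines. Intervals computed as if patients were independent would be too narrow.

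The list of tests also conflicts with the plan's own commitment to the cluster extension of CONSORT.

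**Working it through.** **Inputs (Sample size section).** The trial is sized to "detect a difference of 2.5 points between the two intervention arms with a standard deviation of 5.7", with "an alpha error of 0.05, a beta error of 0.10, and a 20% dropout rate". The ICC is 0.1, with 25 patients per centre, 38 centres (19 per arm) and 932 patients (466 per arm). Sidedness is not stated; a two-sided test reproduces the total.

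**Step 1: reproduce the plan's figure.**
- Patients per arm without clustering: 2 × [5.7 × (1.960 + 1.282) / 2.5]² = 109.2, rounded up to 110.
- Design effect: DE = 1 + (25 − 1) × 0.1 = 3.4.
- With 20% dropout: 109.2 × 3.4 / 0.8 = 464.3, or 110 × 3.4 / 0.8 = 467.5 per arm, against 466 stated.

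The figure reproduces, so the plan itself inflated the sample by 3.4 for clustering. The listed patient-level tests would analyse the data as if that factor were 1.

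**Step 2: analysed patients per centre.** 932 / 38 = 24.5 recruited; 24.5 × 0.8 = 19.6 after dropout.

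**Step 3: true type I error of a test that ignores clustering.** With DE = 1 + (m − 1) × ICC, the naive standard error is too small by a factor √DE. A nominal two-sided 5% test therefore has true size 2 × [1 − Φ(1.96 / √DE)].

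For ICC 0.1 and m = 19.6: DE = 1 + 18.6 × 0.1 = 2.86, √DE = 1.69, 1.96 / 1.69 = 1.16, size = 24.6%.

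| ICC | DE, m = 19.6 | Type I error | DE, m = 25 | Type I error |
|---|---|---|---|---|
| 0.10 | 2.86 | 24.6% | 3.40 | 28.8% |
| 0.05 | 1.93 | 15.8% | 2.20 | 18.6% |
| 0.02 | 1.37 | 9.4% | 1.48 | 10.7% |
| 0.01 | 1.19 | 7.2% | 1.24 | 7.8% |

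Only the first row uses an ICC from the protocol. The other rows are assumptions that show the range.

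**Step 4: simulation check.** The setting was no true effect, 19 centres per arm, ICC 0.1 and 6,000 replicates.

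| Test | 20 per centre | 25 per centre |
|---|---|---|
| t test on patients | 24.6% | 28.9% |
| Mann-Whitney on patients | 23.6% | 28.0% |
| Chi-square on patients | 25.0% | 29.3% |
| t test on the 38 centre means | 5.1% | 4.8% |

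The formula is confirmed, and a simple cluster-level test holds its level. Log-rank and Breslow tests were not simulated. The same mechanism applies to them, but the size of the inflation under censoring was not checked.

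**Step 5: which outcomes have a named clustered analysis?**

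| Outcome | Named patient-level test | Named clustered analysis |
|---|---|---|
| Disability, pain, quality of life and other scales | t or Mann-Whitney | Multilevel linear |
| Satisfaction (0-10 scale) | t or Mann-Whitney | Plausibly multilevel linear |
| Episode duration, return to work | Log-rank, Breslow | Multilevel Cox |
| Sick leave yes/no | Chi-square or Fisher | None named |
| Medication prescription | Chi-square or Fisher, as the general tests for categorical data | None named |
| RRR, NNT | None named | None named |

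**The case against.** The best defence is that the plan knows it is a cluster trial. The multilevel models are introduced expressly to account for cluster randomisation and to assess the intervention effect. The general sentence on regression for clustered data is not limited to the scales, and the Discussion repeats that cluster-specific methods will be used because centres were randomised. The patient-level tests are labelled unadjusted, and the 5% level is set for the models only. On this reading they are a preliminary step, and the model form for binary outcomes is a detail that a condensed article may leave to a fuller document.

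Much of this stands. A reader might infer that the trial's main conclusions rest on naive tests with a 25% false-positive rate throughout. The document does not support that: the primary disability outcome, the other scales, episode duration and return to work all have a planned clustered analysis. Nor are the log-rank and Breslow tests planned at every assessment; that phrase belongs to the t, Mann-Whitney, chi-square and Fisher tests.

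The defence does not dispose of the point. The unadjusted tests are named as between-group comparisons and are nowhere called descriptive. The multilevel linear models also carry baseline scores and other covariates, so the only unadjusted arm comparison named for the scales is the one that ignores clustering. The general sentence on regression names no model for a binary outcome, whereas chi-square and Fisher are named. This is a matter of what the article states, not of detail left to another document.

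**Conclusion.** The concern holds in limited form. The patient-level tests are wrong as written for a trial that randomises centres, and they conflict with the plan's own sample-size assumption and reporting standard. The consequence differs by outcome. For the scales and time-to-event outcomes a valid analysis sits alongside, and the defect is that nothing says which result governs. For sick leave (yes/no) and medication prescription, and for RRR and NNT, no clustered method is named at all.

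At the trial's own ICC, a nominal 5% test that ignores clustering would reject a true null about 25% of the time after the planned dropout and about 29% at 25 per centre. That ICC was assumed for change in disability score. The protocol gives none for the binary outcomes, where the gap is widest, so 25-29% should not be read as their error rate. A fair statement for them is a range: 16-19% if the ICC is 0.05, 9-11% if 0.02. The calculation assumes equal centre sizes.

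**What to change.** Amend the Statistical Analysis section as follows:

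- **Unadjusted arm comparisons.** Replace the patient-level tests with models containing arm, time and the randomisation stratum, with a centre random effect: linear for scales, logistic (or GEE clustered on centre) for sick leave and medication prescription. Tests on centre-level summaries are an acceptable alternative.
- **RRR and NNT.** State that their intervals will allow for clustering.
- **Time to event.** Base inference on the arm effect from the multilevel Cox model already planned, or on a log-rank test with cluster-robust variance. Show Kaplan-Meier curves without a log-rank or Breslow p-value that ignores clustering.
- **Precedence.** State that the clustered result governs wherever two analyses of one outcome are reported.

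The cost is minor rewording and one added model type. Intervals will be wider than the naive ones, by a factor of √2.86 = 1.69 at ICC 0.1 and less at a lower ICC. For the primary outcome the sample size has already been inflated for this, so no planned power is lost.

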**Methods/Design:**

A Cluster randomised clinical trial will be conducted in 38 Primary Health Care Centres located in Barcelona, Spain and its surrounding areas. The centres are randomly allocated to the multidisciplinary intervention or to usual clinical care. Patients between 18 and 65 years old (n = 932; 466 per arm) and with a diagnostic of a non-specific sub-acute low back pain are included. Patients in the intervention group are receiving the recommendations of clinical practice guidelines, in addition to a biopsychosocial multidisciplinary intervention consisting of group educational sessions lasting a total of 10 hours. The main outcome is change in the score in the Roland Morris disability questionnaire at three months after onset of pain. Other outcomes are severity of pain, quality of life, duration of current non-specific low back pain episode, work sick leave and duration, Fear Avoidance Beliefs and Goldberg Questionnaires. Outcomes will be assessed at baseline, 3, 6 and 12 months. Analysis will be by intention to treat. The intervention effect will be assessed through the standard error of measurement and the effect-size. Responsiveness of each scale will be evaluated by standardised response mean and receiver-operating characteristic method. Recovery according to the patient will be used as an external criterion. A multilevel regression will be performed on repeated measures. The time until the current episode of low back pain takes to subside will be analysed by Cox regression.

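### The protocol defines the intervention effect in two competing ways, and one of them (SEM and effect-size) cannot be relied on to contrast the intervention with usual care

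*Protocol article*

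**What the plan says.** The protocol article describes the effect of the intervention in three places.

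- **Abstract, Methods/Design:** "The intervention effect will be assessed through the standard error of measurement and the effect-size". A multilevel regression on repeated measures is listed there too, but it is not tied to the intervention effect.
- **Statistical Analysis, group-level change:** with the stated aim of detecting change in groups, "the intervention effect will be calculated through the effect-size for each questionnaire and at each assessment". The method is given by citation only, with no formula.
- **Statistical Analysis, clustered data:** multilevel linear regression on repeated measures "will be used to assess the effect of intervention and to investigate the factors that influence each of the outcome scales". Intervention and time are fixed effects, centre and individual are random effects, and baseline scores are adjusted for.

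The Statistical Analysis section uses the SEM differently from the Abstract: individual change scores are compared with it when deciding what counts as an important change in one person. The section also plans comparisons of change scores: "Continuous data for change in scores from baseline will be compared between groups and for each group". For pre-post change it adds: "The paired t-test for difference will be used to compare the change between pre- and post- intervention". No sentence ranks these quantities or says which one is the trial's estimate of effect.

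**The concern.** A randomised trial against usual care answers its question through a difference between arms. The SEM contains no such difference. An effect-size for change in a group contains none either, if it is computed within each arm.

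This matters in low back pain because patients improve under ordinary care. The Background cites a study in Spanish primary care centres in which, after two months of treatment, pain continued in 37% and had worsened in 10%. That leaves 53% in neither category if the two figures are separate, or 63% if the 10% lies within the 37%. Those patients were not selected as sub-acute and the figures are not RDQ scores, but they show that the authors expect substantial recovery without the new programme. A within-arm index adds that recovery, and any regression to the mean, to whatever the intervention contributes.

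At stake is which number is reported as the main result. A reader of the Abstract alone would expect an SEM and an effect-size.

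**Working it through.** **1. What the trial is sized for.** Inputs from Sample size: difference between arms 2.5 RDQ points, SD 5.7, alpha 0.05 (two-sided assumed), beta 0.10, ICC 0.1, 25 patients per centre, 20% dropout.

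- Per arm, unclustered: 2 × [5.7 × (1.960 + 1.2816) / 2.5]² = 109.2
- Design effect: 1 + (25 − 1) × 0.1 = 3.4
- Per arm with clustering and dropout: 109.2 × 3.4 / 0.80 = 464.3, or 110 × 3.4 / 0.80 = 467.5 if 109.2 is first rounded up
- Stated: 466 per arm, 932 in total. The figure is reproduced closely. 932 / 25 = 37.3, which fits 38 centres.

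The design therefore rests on a between-arm contrast, with standardised size 2.5 / 5.7 = 0.44.

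**2. The SEM.** It is the SD of a score multiplied by the square root of (1 − reliability). Treatment arm does not enter the formula, so no value of the SEM estimates an effect. The Statistical Analysis section agrees in practice, since it applies the SEM only to individuals. The Abstract sentence conflicts with it.

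**3. The effect-size, if read as within-arm change.** Let both arms improve by c points and let the intervention add d points.

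- Within-arm effect-size, intervention arm: (c + d) / SD
- Between-arm effect-size: [(c + d) − c] / SD = d / SD
- Excess of the first over the second: c / SD

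The values of c are assumptions, because the protocol gives no expected change under usual care. The SD is taken as 5.7 from Sample size, which does not say whether it is a baseline SD or an SD of change. With a true effect of d = 0:

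| Shared improvement c (RDQ points) | Within-arm effect-size, each arm | Between-arm effect-size |
|---|---|---|
| 1 | 1 / 5.7 = 0.18 | 0 |
| 2.5 | 2.5 / 5.7 = 0.44 | 0 |
| 4 | 4 / 5.7 = 0.70 | 0 |
| 5 | 5 / 5.7 = 0.88 | 0 |

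A shared recovery of 2.5 points gives the same value as the planned treatment effect. That match does not depend on 5.7: it holds for any SD used in both ratios. If d = 2.5 and c = 2.5, the within-arm value is 5 / 5.7 = 0.88, twice the between-arm 0.44.

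**4. Is the effect-size within-arm?** The text points that way without settling it. The effect-size is introduced for change in groups, directly after a paragraph on change in individuals, and is followed by the standardised response mean (SRM), which is computed from baseline to each assessment in each arm. The protocol does not say explicitly that the effect-size is also computed per arm.

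**The case against.** The strongest reply is that the between-arm comparison is planned several times over. The main objective is framed against usual care, and the sample size is for a difference between arms. Change scores are compared between groups, unadjusted between-group tests are run at each assessment, and the multilevel model has intervention as a fixed effect. If both arms recovered equally, these analyses would be expected to show no difference. This stands. A reader might infer that shared recovery will be reported as benefit, or that the randomised comparison is given up. The document supports neither.

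Two further inferences also fail. A reader might take the paired t-test to be a third definition of the intervention effect, but the protocol never gives it that label. A reader might also suppose that benefit will be concluded from significance in one arm and not in the other, but no such rule appears.

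It is also fair to say that the formula is only cited, and that the reference to groups may mean group-level as opposed to individual-level change. The within-arm reading is therefore plausible, not proven.

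The reply does not remove the conflict. The Abstract and the Statistical Analysis section attach the intervention effect to quantities other than the model estimate, one of which cannot measure it. A separate analysis plan might set a priority, but the published sentences would still be wrong as they stand.

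**Conclusion.** The point holds as a wrong and competing definition of the headline effect, with no stated order of priority. That the SEM cannot serve as the intervention effect needs no assumption. That the effect-size could credit shared recovery to the intervention depends on reading it as within-arm change. On that reading, with SD 5.7 and shared improvements of 1 to 5 points, it would show 0.18 to 0.88 when the true effect is 0, passing through the design value of 0.44 at 2.5 points. These figures illustrate what could happen if the effect-size were taken as the treatment effect. They do not predict what the trial will report, because valid between-arm analyses are planned alongside. The sample size is unaffected.

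**What to change.** In the Abstract and in the group-level paragraph of Statistical Analysis, define the intervention effect as the between-arm difference in RDQ at three months, estimated from the planned multilevel model (baseline RDQ adjusted, centre as a random effect), with a 95% CI. Reading a three-month difference from a repeated-measures model requires the intervention-by-time term, which the section already intends to study.

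If a standardised value is wanted, divide that between-arm difference by the pooled baseline SD and state the formula.

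Remove the SEM from the Abstract sentence on the intervention effect. Keep the within-arm effect-size, SRM, SEM and paired tests, labelled as descriptive or as serving the responsiveness objective, and state that they are not used to judge the intervention.

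The cost is a few sentences. Patient numbers, centres, data collection and the model stay as planned. The change should be made before the data are analysed.

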### Other non-pharmacological therapeutic measures and Patient Compliance

During the intervention period, other non-pharmacological therapeutic measures which differ from those stated in the intervention design will be advised against. However, in the case of non-pharmacological therapeutic measures occurring, they will be registered and included in the analysis.

In the follow-up visits at 3, 6 and 12 months, we will ask about the patient compliance of recommendations of treatment and the questionnaires will be completed. Furthermore, if the patient is unable to attend the follow-up visits, the data collection will be carried out by telephone call.

Compliance to the group sessions will be assessed by registering the number of group sessions that patients attend.

To ensure patients' adherence to the group sessions, they will be asked a time preference (morning or afternoon) to attend the sessions. One week prior to the group session, they will receive a phone call to report the date, time and location of the session and on the day before, an SMS message with the same information will be sent.

At the end of the study, the control group will receive the compact disc of Jacobson's progressive relaxation technique, the educational booklet "The Back Manual" and the audiovisual.

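### The model for the intervention effect also adjusts for other scale scores that are not limited to baseline and are selected by significance, so its coefficient may not be the total intention-to-treat effect

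*Protocol article*

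**What the plan says.** Protocol article, Statistical Analysis: a multilevel linear model for the repeated measures "will be used to assess the effect of intervention and to investigate the factors that influence each of the outcome scales at each time point". One model therefore serves two purposes.

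Its adjustment list begins "adjusting for baseline scores, baseline characteristics of patients (socio-demographic, clinical and professional" and ends "and the other scale scores if they are found to affect outcomes significantly over time". The first two items carry the word baseline; the third does not. On structure, the section states: "The PHCC and the individual will be considered as random effects and intervention and time as fixed effects".

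Two other places bear on the point:

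- Randomisation: "randomisation was conducted stratifying by percentage of immigrants from developing countries registered in each district", and "We consider two strata, less than and more than 15% immigrants". The model description does not name this factor.
- Other non-pharmacological therapeutic measures and Patient Compliance: if such measures occur, "they will be registered and included in the analysis". How they enter is not stated.

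Outcomes lists pain and SF-12 with the Roland Morris questionnaire (RDQ) as primary outcomes, and fear-avoidance and Goldberg anxiety/depression as secondary. Table 4 schedules all of them after baseline.

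**The concern.** The main objective and the intention-to-treat principle call for the total effect of offering the programme. A model that also contains follow-up scores of the other scales estimates something else: the difference in RDQ between patients who have the same pain, fear-avoidance, mood or quality of life at follow-up. The programme is designed to shift those variables. Table 2 gives the psychologist's sessions the task of modifying thoughts that affect emotions and pain, and the Outcomes section itself asserts that fear-avoidance influences disability. SF-12 contains physical function and bodily pain, so adjusting RDQ for concurrent SF-12 comes close to adjusting disability for itself. Because the rule covers every outcome scale, pain could likewise be adjusted for disability.

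Separately, letting significance in the trial data decide which scales enter means that the effect model is not fixed in advance, whichever visit the scores come from.

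No other planned RDQ comparison fills the gap. The unadjusted comparisons are t, Mann-Whitney, chi-squared or Fisher tests, which ignore the centres. At the plan's own design effect of 3.4, a naive standard error is too small by a factor of √3.4 = 1.84.

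**Working it through.** **1. The plan's own figure.** Inputs from Sample size: difference 2.5, SD 5.7, alpha 0.05 (taken as two-sided), power 0.90, ICC 0.1, 25 per centre, 20% dropout.

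- Per arm, unclustered: 2 × (5.7 × (1.960 + 1.282) / 2.5)² = 109.24, i.e. 110.
- Design effect: 1 + 24 × 0.1 = 3.4.
- 110 × 3.4 / 0.8 = 467.5, or 109.24 × 3.4 / 0.8 = 464.3. The stated 466 per arm (932) is reproduced to within rounding.
- Effective number per arm: 466 × 0.8 / 3.4 = 109.6. SE = 5.7 × √(2/109.6) = 0.770. Power = Φ(2.5/0.770 − 1.96) = 90%.

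**2. Adjusting for one concurrent scale.** In a linear model with equal slopes in both arms, adjusted effect = total effect − slope × effect on the other scale. With r the within-arm correlation of RDQ with that scale, and dM the intervention effect on that scale in SD units:

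adjusted effect = 2.5 − r × 5.7 × dM

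The article gives neither r nor dM. Assumed ranges: r = 0.3 to 0.7 and dM = 0.2 to 0.44. The upper dM equals the planned standardised effect on RDQ, 2.5/5.7 = 0.44. For power, the SE is multiplied by √(1 − r²), because the covariate also reduces residual variance.

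| r | dM | adjusted effect | removed | power | simulated effect |
|---|---|---|---|---|---|
| 0.3 | 0.20 | 2.16 | 14% | 83.6% | 2.17 |
| 0.3 | 0.30 | 1.99 | 21% | 77.2% | 2.01 |
| 0.3 | 0.44 | 1.75 | 30% | 66.3% | 1.74 |
| 0.5 | 0.20 | 1.93 | 23% | 82.5% | 1.93 |
| 0.5 | 0.30 | 1.65 | 34% | 69.4% | 1.65 |
| 0.5 | 0.44 | 1.25 | 50% | 46.4% | 1.24 |
| 0.7 | 0.20 | 1.70 | 32% | 87.2% | 1.69 |
| 0.7 | 0.30 | 1.30 | 48% | 65.9% | 1.35 |
| 0.7 | 0.44 | 0.74 | 70% | 27.2% | 0.75 |

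The last column is the mean of 600 simulated trials (38 centres of 20, ICC 0.1, one follow-up visit, one other scale), shown as the size of the reduction in RDQ.

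**3. Baseline score instead.** In the same simulations, adjusting for the baseline value of the other scale gave 2.47 to 2.54, so the 2.5-point effect is preserved.

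**4. The stratum.** Analysed per centre: 466 × 0.8 / 19 = 19.6. Between-centre variance is 0.1 × 5.7² = 3.249; within-centre variance is 0.9 × 5.7² = 29.241. If the stratum explains a share x of the between-centre variance (assumed):

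SE = √(2 × (3.249 × (1 − x) + 29.241/19.6) / 19)

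- x = 0: 0.706
- x = 0.1: 0.682 (3.5% lower)
- x = 0.2: 0.656 (7% lower)
- x = 0.3: 0.630 (11% lower)

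The starting SE differs from the 0.770 in step 1 because it uses 19.6 completers per centre rather than 25. The two steps should not be combined.

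**The case against.** The text never says that the other scores are follow-up values. A baseline fear-avoidance score can affect outcomes over time, and the earlier phrase about baseline scores may mean only the baseline of the outcome being modelled. Table 4 gives this reading some support: fear-avoidance and Goldberg are not collected at 6 months, so they could not be concurrent covariates at every visit. This stands as a reason for doubt, but it does not settle the matter. Pain and SF-12 are collected at every visit, and nothing restricts the clause to baseline. On the baseline reading the selection by significance remains.

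A reader might also infer three stronger things that the document does not support:

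- That the intervention effect is adjusted away. Only part would be removed, by an amount that rests on unstated correlations; with dM = 0 nothing is removed. Nor is shrinkage certain: if a scale moved the other way, the coefficient would grow, and unmeasured common causes of the scale and RDQ can distort it in either direction. Power losses computed with the SE held at 0.770 are also too large: at r = 0.5 and dM = 0.3 that gives 57%, against 69% when the smaller residual variance is counted.
- That co-interventions are covariates in the effect model. The statement that they will be included in the analysis does not say how, and the covariate list does not name them.
- That leaving out the stratum damages the estimate. It causes no bias, and it costs precision only if the stratum is prognostic. The sentence on random and fixed effects is not exhaustive either, since it also omits the baseline scores. A journal article may leave this term to the analysis plan.

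**Conclusion.** The point holds in a limited form. The only cluster-adjusted model described for RDQ carries a covariate rule that is not confined to baseline and works by significance in the trial data. Read naturally, it conditions on post-allocation outcomes that the programme targets, so its coefficient is not the total intention-to-treat effect and would usually be smaller. Illustratively, 14% to 70% of 2.5 points is removed and power lies between 27% and 87% instead of 90%, for a single concurrent scale with assumed r of 0.3 to 0.7 and dM of 0.2 to 0.44. Read as baseline only, there is no such bias, and the remaining defect is that the effect model is not fixed beforehand. The wording needs correction under either reading. The stratum is a secondary matter of precision: an SE about 3.5% to 11% lower if it explains 10% to 30% of between-centre variance (assumed), and unchanged if it explains none.

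**What to change.** Separate the two purposes of the model.

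- **Intervention effect:** a cluster-adjusted multilevel model with covariates named in advance: the baseline value of the outcome, the randomisation stratum (below or above 15% immigrants), and a short named list of other baseline variables, for example pre-study duration of the episode. If other scales are wanted, state that only their baseline values enter. Use no follow-up scale scores and no selection by significance.
- **Prognostic or mediation analysis:** a separate model, labelled exploratory, for follow-up scale scores and any co-interventions.

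The cost is analysis wording only. All the variables are already collected, and the sample size does not change.
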